#### Monitoring for efficacy

If the overall event rate at interim analysis is higher than the threshold of 10%, the event rate in both treatment groups will be estimated and the between-group risk difference (RD) and its confidence interval will be estimated. To preserve the overall type I error for one interim analysis and the final analysis, the *α* of 0.05 (2-sided) is spent using the Lan-DeMets spending function. At the interim analysis, a 99.95% confidence interval is calculated; at the final analysis, a 95.05% confidence interval is calculated. It is unlikely that at interim analysis, non-inferiority can be declared unless the experimental treatment is superior to active control [26].

#### Monitoring for safety

Safety concerns in this study are twofold: (R1) the efficacy endpoint (MALE) may differ substantially between treatment groups and (R2) mortality may differ between treatment groups. On safety grounds, termination of the trial may be recommended after the interim analysis. However, such assessments may potentially have implications for falsely concluding that there is an adverse effect. No statistical reasons for stopping the trial at interim analysis are declared.

Notation:

*δ*_Int_: between-group risk difference *p*_exp_ − *p*_con_ at 12 months at interim analysis for MALE

*d*_Int_: between-group risk difference *π*_exp_ − *π*_con_ at 12 months at interim analysis for mortality

exp = experimental group, coated devices

con = active control group, uncoated devices

**Table Tabb:** 

Scenario	Reasoning	Interpretation	Action
Interim analysis after 600 patients followed up 12 months (50% of total sample size)			
*p*_total_ ≤ 0.10	Verify assumptions about nuisance parameters	Obtain an estimate of overall MALE event rate at interim. Assumptions about nuisance parameters seem to be realistic.	Continue trial without any changes.
*p*_total_ > 0.10	Safety	Differential MALE event rates between treatment groups could be causing higher event rate than anticipated.	Unblinded estimation of the MALE event rates in each treatment group.
(1) *δ*_Int_ = 0	Efficacy	*p*_exp_ = *p*_con_	Calculate Bayesian predictive probabilities for successful termination of trial. Continue the trial unless otherwise stated by DMB. Based on interim results, the DMB may suggest a sample size increase.
(2) *δ*_Int_ > 0	Efficacy: R1	MALE event rate in the experimental group is considerably higher than in the control group.	Quantification of “how much higher”. DMB discusses stopping for safety reasons.
(3) *δ*_Int_ < 0	Efficacy: R1	MALE event rate in the experimental group is considerably lower than in the control group.	Quantification of “how much lower”. DMB discusses stopping for safety reasons.

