**Fig. 4 Fig4:**
[figure not shown]
Study recruitment

The Clinic of Angiology of the University Hospital of Zurich and the Division of Angiology of the Cantonal Hospital Fribourg currently performs together approximately 1050 peripheral interventions per year. Therefore, assuming that more than 80% of the potentially eligible patients will be finally enrolled in the study, the patient recruitment is expected to last no longer than 30 months with the Last-Patient-Out visit for the 5-year cumulative mortality analysis planned in 2028.

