### Interim analyses {21b}

A single interim analysis with information rate of 50%, i.e., 300 patients per arm, 600 in total, is planned. If at interim the overall event rate exceeds a pre-specified threshold of 10%, the event rate will be estimated in both treatment groups (unblinded).

Following D’Agostino et al. [25] “for efficacy reasons one can argue that there is no real ethical issue with seeing the [non-inferiority] trial to completion from an efficacy perspective”. However, “interim analyses are also important in a non-inferiority trial for safety reasons, either to ensure the experimental treatment is not doing more harm than good (R1), or that it is superior with regard to specific adverse events (R2).”

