**Table Tabc:** 

Continuous safety evaluation, after multiples of 150 patients at 12-month follow-up			
*d*_Int_ ≠ 0	Safety: R2	Unblinded estimation of mortality rates. Assess if mortality rates are different between treatment groups.	How much higher mortality rate in one group compared to the other after 12-month follow-up?

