## Trial status

The first patient has been enrolled in the Sir-PAD study on 3 November 2020. As to 22 December 2021, a total of 396 patients have been enrolled at the Clinic of Angiology of the University Hospital Zurich. The site initiation visit of the second center (Department of Internal Medicine and Division of Angiology, Cantonal Hospital Fribourg) is planned in January 2022. The completion of patient recruitment (last patient in) is expected in Q4 2023. The completion of the 5-year follow-up (last patient last visit) is expected by the end of 2028.

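### Limb events are one of two declared safety concerns, but the only stated by-arm comparison is conditional and comes when about 79–90% of patients are already randomised

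*Protocol article*

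**What the plan says.** All references are to the protocol article.

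- **Two concerns.** Monitoring for safety states: "Safety concerns in this study are twofold: (R1) the efficacy endpoint (MALE) may differ substantially between treatment groups and (R2) mortality may differ between treatment". It adds: "On safety grounds, termination of the trial may be recommended after the interim analysis".
- **MALE (R1).** Interim analyses {21b} says: "A single interim analysis with information rate of 50%, i.e., 300 patients per arm, 600 in total, is planned". The scenario table under Monitoring for safety times it as "Interim analysis after 600 patients followed up 12 months (50% of total sample size". The by-arm comparison is conditional: "If at interim the overall event rate exceeds a pre-specified threshold of 10%, the event rate will be estimated in both treatment groups (unblinded"). At or below 10%, the table's action is to continue unchanged.
- **Mortality (R2).** A second table is headed "Continuous safety evaluation, after multiples of 150 patients at 12-month follow-up". Its single row concerns the mortality difference.
- **Other reviews.** Assessment of safety outcome (under {18a}) has the committee evaluate safety data, not further specified, each time another 150 patients have been included. The section on the data monitoring committee {21a} places the review after 12-month follow-up of multiples of 150, and lets the board recommend continuing or terminating.
- **Early outcome.** Safety outcomes (under {12}) lists death or MALE within 30 days. No review passage names it.
- **Recruitment.** Recruitment {15}: "the patient recruitment is expected to last no longer than 30 months". Trial status: "The completion of patient recruitment (last patient in) is expected in Q4 2023". Trial status also gives the first enrolment on 3 November 2020 and 396 patients by 22 December 2021.

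**The concern.** The protocol fixes who looks at what and when, and it gives its two declared safety concerns unequal schedules without a stated reason. Mortality is compared by arm repeatedly. Limb events are compared once at most, after 600 patients have 12 months of follow-up.

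Treatment is a single procedure immediately after randomisation, so a safety look protects only patients not yet randomised. If most are already treated, a recommendation to stop for limb harm helps few. The pooled-rate condition adds a second weakness. If the control rate is well below the planned 10%, a large relative excess in the coated arm can leave the pooled rate under the threshold, and the arms are then not compared at this look.

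**Working it through.** **Planning figures.** With 10% MALE in both arms, a 5-point margin, one-sided 2.5% and 80% power:

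n per arm = (1.960 + 0.842)² × 2 × 0.10 × 0.90 / 0.05² ≈ 566, so 1132 in total; 1132 / 0.95 ≈ 1192, against the stated 1200.

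The sample size reproduces, and 600 of 1200 is the stated 50%.

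**Share randomised when the 600th patient reaches 12 months.** Formula: (600 + accrual over the next 12 months) / 1200, with constant accrual within each scenario.

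| Scenario | Accrual | Randomised at the look |
|---|---|---|
| First centre's observed rate continues | 396 / 414 days = 0.957 per day | 600 + 365 × 0.957 = 949 (79%) |
| Last patient in on 31 Dec 2023 | 804 / 739 days = 1.088 per day | 600 + 365 × 1.088 = 997 (83%) |
| Last patient in on 1 Oct 2023 | 804 / 648 days = 1.241 per day | 600 + 365 × 1.241 = 1053 (88%) |
| Uniform 30 months | 1200 / 30 = 40 per month | 600 + 12 × 40 = 1080 (90%) |

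Here 804 = 1200 − 396 is the number still to recruit after 22 December 2021. The scenarios differ partly because the article does: November 2020 to Q4 2023 is about 35 to 38 months, not 30. Reading Recruitment {15} literally (80% of 1050 interventions a year, 70 per month) would put all 1200 in before the look, but observed accrual of about 29 per month contradicts that rate.

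Patients not yet randomised at the look: 1200 − 1080 = 120 to 1200 − 949 = 251. The 30-day window on the 1-year visit could add about 29 to 39 more randomised patients, and data cleaning more again.

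**Comparison with the mortality reviews.** If recruitment ends in mid-November 2023, reviews triggered by 12-month follow-up of 150, 300 and 450 patients fall at about 521, 703 and 874 randomised (43%, 59% and 73%).

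**The pooled-rate condition.** With 300 per arm, more than 60 events in 600 are needed. Exact binomial probabilities of crossing the threshold, for illustrative true rates (apart from 10% in both arms, these are not in the article):

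| Control | Coated | P(pooled rate > 10%) |
|---|---|---|
| 5% | 10% | 0.010 |
| 6% | 12% | 0.175 |
| 10% | 10% | 0.466 |
| 10% | 15% | 0.967 |

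The condition works if the control rate is near 10%. If the control rate is about half that, a doubling of limb events would usually not trigger a by-arm comparison.

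**The case against.** The strongest case against is that the board is not blind to limb harm before the interim. The general reference to safety data is wider than mortality, and the 30-day composite is a listed safety outcome, so it can be read as included. The board may recommend termination at any of its 150-patient reviews. An unplanned major amputation would ordinarily meet the serious adverse event definition and reach the sponsor within 24 hours. An events committee meets regularly, and the trial is open-label. Report contents are also often left to a charter or the full protocol, neither of which is shown.

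Much of this stands, and it rules out two stronger readings. A reader might infer that the 30-day composite is excluded from review, or that limb harm could not lead to action until nearly everyone is treated. The documents support neither. A reader might also take the 2 of 38 early major amputations in the first-in-human study as a sign of device harm. The article attributes them to foot sepsis, and it reports no control arm, so they are not used here.

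The reply is narrower. Individual event reports are not a by-arm comparison with denominators. The one passage that specifies what the repeated review compares names mortality alone. The general passage times reviews at inclusion, while two others time them at 12-month follow-up.

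Early looks are also imprecise. At 75 per arm, assumed 30-day rates of 5% and 10% would be distinguished at two-sided 5% with power of only about 21% (normal approximation). That argues for a descriptive display rather than a test.

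**Conclusion.** The concern holds in limited form. The only by-arm MALE comparison that the article specifies before the final analysis is conditional on a pooled rate above 10%. It falls when 949 to 1080 of 1200 patients (79–90%) are randomised, so a stop at that point would spare at most about 120 to 250. Early limb outcomes are collected but named in no review, and the passages conflict on when reviews occur. Action before the interim is possible, but no specified by-arm limb comparison supports it.

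The share rests on constant accrual within each scenario and on the article's recruitment figures. The trigger probabilities rest on illustrative event rates. A board charter or the full protocol may already specify more. The point is a worthwhile, inexpensive improvement to monitoring and does not affect the validity of the primary analysis.

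**What to change.** 1. Add an R1 row to the continuous safety evaluation table. At each 150-patient review the board sees 30-day death or MALE by arm, with major amputation shown separately, for every patient at least 30 days past randomisation, whatever the pooled rate.
2. State that the display is descriptive and confidential to the board, supports no efficacy claim and spends no alpha. Confidentiality {27} gives the sponsor-investigator and investigators access to data sets during the study, so the restriction must be explicit.
3. Reconcile Assessment of safety outcome with the continuous evaluation table and the data monitoring committee section on when the reviews take place and which outcomes they cover.
4. Keep the 600-patient interim for its efficacy and event-rate purposes.

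The cost is a few lines in reports already planned, from data already collected, plus the wording on access. The downside is low precision at early looks and a somewhat higher chance of a false alarm, a risk that the plan already accepts for mortality.

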**Table Tabc:** 

Continuous safety evaluation, after multiples of 150 patients at 12-month follow-up			
*d*_Int_ ≠ 0	Safety: R2	Unblinded estimation of mortality rates. Assess if mortality rates are different between treatment groups.	How much higher mortality rate in one group compared to the other after 12-month follow-up?

### Methods for additional analyses (e.g., subgroup analyses) {20b}

Multivariable logistic regression for the outcome MALE event will be used to estimate an adjusted treatment effect, given the stratification variables. The following subgroups are pre-specified for analysis of heterogeneity of effects: age ≥ 75 vs. < 75, men vs. women, patients with elective re-vascularization (Fontaine I–II) vs. critical re-vascularization (Fontaine > II), patients with 1 vs. more than 1 level intervention, de novo lesion vs. restenosis, total occlusion vs. partial occlusion, distal vs. proximal lesions. If there is evidence for a differential treatment effect within subgroups (i.e., *p*-value of interaction test < 0.05), the treatment effect will be reported within subgroups as odds ratios or hazard ratios for time-to-event outcomes.

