### Intervention description {11a}

The Magic Touch PTA device is a sirolimus-coated balloon catheter indicated for the treatment of stenotic lesions of infra-inguinal or infra-popliteal arteries and consists of two components: (1) a PTA balloon catheter coated with (2) polymer-free formulation containing the sirolimus drug as an active ingredient in an encapsulated phospholipid excipient. The drug dose per mm^2^ balloon surface is 1.27 μg. POBA is performed for vessel preparation (pre-dilatation). In addition, in the experimental group, in a second step, patients will receive target lesion treatment with the Magic Touch PTA sirolimus-coated balloon (Concept Medical B.V., Hoevelaken, The Netherlands). All balloons will be inflated for a duration of 120 s at nominal pressure. Nominal pressure is defined as the inflation pressure required for reaching the device-specific diameter.

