### Relevant concomitant care permitted or prohibited during the trial {11d}

Provisional stent placement is used in case of severe arterial dissection and/or persisting (flow-limiting) lumen compromise following balloon angiography necessitating a stent for mechanical scaffold. Concomitant in- and outflow disease may be treated upon discretion of the interventionist using uncoated devices. All concomitant treatments have to be recorded in the CRF.

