## Assignment of interventions: allocation

### Sequence generation {16a}

After the angiographic screening and definition of the target lesion, but prior to any therapeutic intervention, each eligible patient will be assigned to one of the two open treatment arms of this trial by an online randomization tool. This generation of the randomization sequence was generated before the start of the study outside the platform, REDCap, serving for data collection and used other software (R). Randomization will be stratified according to the stage of disease, namely elective re-vascularization (Fontaine stages I–II) vs. critical rescue re-vascularization (Fontaine stages III–IV), and study center. A block randomization will be done using an online random tool (REDCap, Vanderbilt University, v9 1.0).

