### Concealment mechanism {16b}

Allocation will be concealed and treatment will be done immediately thereafter during the same angiographic session.

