## Assignment of interventions: blinding

### Who will be blinded {17a}

The trial is conducted as an open-label study.

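### The single-level versus multi-level subgroup is worded by treatment delivered after open allocation, so its contrasts between arms can be biased; it should be defined from the angiogram taken before randomisation

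*Protocol article*

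**What the plan says.** The section on additional analyses (item 20b) pre-specifies seven subgroup factors. Six are patient or lesion features that can be fixed before allocation: age, sex, Fontaine stage, de novo lesion or restenosis, degree of occlusion, and lesion location. The seventh is "patients with 1 vs. more than 1 level intervention". If an interaction test gives p < 0.05, "the treatment effect will be reported within subgroups as odds ratios or hazard ratios for time-to-event outcomes".

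Four other sections settle when the number of treated levels is determined:

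- Sequence generation (16a): randomisation takes place "After the angiographic screening and definition of the target lesion, but prior to any therapeutic intervention".
- Concealment mechanism (16b): "treatment will be done immediately thereafter during the same angiographic session".
- Who will be blinded (17a): "The trial is conducted as an open-label study".
- Concomitant care (11d): "Concomitant in- and outflow disease may be treated upon discretion of the interventionist using uncoated devices".

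The number of levels is not a stratification factor; the strata are Fontaine stage and centre.

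**The concern.** A subgroup analysis compares the arms fairly only if membership cannot be influenced by the arm. Here the order is diagnostic angiogram, open allocation, then a discretionary decision on further levels. The number of levels treated is therefore a post-randomisation variable.

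The arms also differ in procedure: "in the experimental group, in a second step, patients will receive target lesion treatment with the Magic Touch PTA sirolimus-coated balloon". An extra step in one arm is a conceivable reason for operators to treat additional disease more or less readily in that arm. If they do, the multi-level subgroup in one arm holds patients of different prognosis from the multi-level subgroup in the other, and likewise for the single-level subgroups.

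At stake is the secondary objective of testing whether efficacy is maintained across important subgroups. For this factor, a difference in operator behaviour could be read as a property of the device.

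**Working it through.** **Plan's own figure.** No stated figure bears directly on this subgroup. The sample size supplies the event rate and arm size used below, and it reproduces: n per arm = (1.96 + 0.8416)² × 2 × 0.10 × 0.90 / 0.05² ≈ 566, total 1132. With 5% drop-out, 1132 / 0.95 ≈ 1192, against 1200 stated. The illustrations use 600 per arm and no true treatment effect. All patient mixes, risks and treatment shares are assumptions.

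**Scenario A: extra levels withheld from the least sick (simulation).** Half of patients have multi-level disease. MALE follows a logistic model with intercepts from 6% (single-level) and 14% (multi-level), each lowered by 0.2 on the logit scale, plus a severity term of 0.6 per SD. The correlation between severity and having extra levels treated is 0.7. Overall MALE is about 9.4%. Extra levels are treated in 80% of control patients with multi-level disease.

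| Sirolimus arm treated | Spurious RD, multi-level | Spurious RD, single-level | OR, multi / single | Interaction false-positive rate |
|---|---|---|---|---|
| 60% | +1.4 points | +0.6 points | 1.12 / 1.10 | 5.0% |
| 50% | +2.3 points | +1.0 points | 1.19 / 1.17 | 5.0% |

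On the odds-ratio scale both subgroups shift together (1.12 / 1.10 ≈ 1.02 and 1.19 / 1.17 ≈ 1.02), so the interaction test stays at its nominal level. With subgroups defined by diseased levels, the risk differences are zero to within 0.1 point.

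**Scenario B: other patterns of who gets extra treatment (analytic).** Three groups k with share w and risk r: severe multi-level (0.20, 22%), mild multi-level (0.20, 10%), single-level (0.60, 6%). Overall risk is 0.044 + 0.020 + 0.036 = 10%. With q the fraction of each group treated at more than one level (zero for single-level disease):

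- share in the multi-level subgroup: m = Σ w q
- its risk: Σ w q r / m
- risk in the single-level subgroup: (0.10 − Σ w q r) / (1 − m)
- interaction: z = |ln(OR multi / OR single)| / SE, with SE² = Σ 1/(n p (1 − p)) over the four cells
- false-positive rate: 1 − Φ(1.96 − z) + Φ(−1.96 − z)

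Control arm, q = 95% (severe) and 90% (mild): m = 0.19 + 0.18 = 0.37; risk (0.0418 + 0.0180)/0.37 = 16.16%; single-level risk 0.0402/0.63 = 6.38%.

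Worked example, sirolimus arm q = 40% and 80%: m = 0.08 + 0.16 = 0.24; risk 0.0336/0.24 = 14.0%; single-level risk 0.0664/0.76 = 8.74%. The odds ratios are 0.84 and 1.41, their ratio 0.60, SE 0.40, z = 1.26, and the false-positive rate 24.3%.

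| Sirolimus arm q (severe / mild) | OR multi | OR single | False-positive rate |
|---|---|---|---|
| 95% / 90% (as control) | 1.00 | 1.00 | 5.0% |
| 95% / 50% | 1.13 | 1.07 | 5.2% |
| 95% / 20% | 1.29 | 1.11 | 6.7% |
| 50% / 50% | 0.99 | 1.36 | 12.4% |
| 60% / 90% | 0.90 | 1.27 | 13.9% |
| 40% / 80% | 0.84 | 1.41 | 24.3% |

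The interaction test is disturbed little when only milder patients lose the extra treatment, and appreciably when severe patients lose it in one arm.

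**The case against.** Five things can be said for the plan.

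- Nothing in the article shows that operators will treat extra levels differently by arm. Concomitant disease gets uncoated devices in both arms, in one session, under standard care. The larger error rates need extra treatment of severe patients to fall from 95% to between 40% and 60%. This stands, and small arm differences give small bias.
- Subgroup effects are to be reported only after an interaction p < 0.05. In Scenario A that happens no more often than chance, so the biased estimates would seldom be shown. The spurious differences are also smaller than their standard errors (about 3.6 to 3.8 points in the multi-level subgroup, 1.7 in the single-level one). This stands too.
- The label is undefined in a condensed article, and the full protocol or analysis plan may code it from the diagnostic angiogram. That is possible and lowers confidence. But the printed label names the intervention, and reading it as disease extent would amount to the change proposed here.
- Concomitant treatments are recorded in the CRF, so an imbalance could be seen. Seeing it would not restore a randomised comparison.
- Only one of seven exploratory factors is affected. This stands.

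A reader might infer that the interaction test is necessarily distorted, that the subgroup objective will give a wrong answer for this factor, or that the main result is compromised. The documents support none of these. The first depends on which patients get extra levels treated, the second on behaviour that is not shown, and the third fails because the primary risk difference does not use this variable.

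**Conclusion.** The point holds as a possibility of bias, at minor severity. As printed, the subgroup is defined by a decision taken after open allocation, so its contrasts between arms are not protected by randomisation. If extra levels are treated at different rates by arm, within-subgroup effects can be biased by roughly 1 to 2 points in the multi-level subgroup and 0.6 to 1 point in the single-level one under Scenario A. The interaction error rate can range from 5% to about 24%, depending on which patients are affected. These sizes rest wholly on assumed patient mixes and treatment shares. The non-inferiority test, the hierarchical superiority tests, the sample size and the other six subgroups are untouched.

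**What to change.** Redefine the factor as one versus more than one diseased level (at least 50% stenosis) on the diagnostic angiogram before randomisation, entered in the eCRF before the allocation is shown. Angiographic screening already precedes randomisation, so the information arises for every patient. For those already enrolled (396 of the planned 1200 at the reported date of 22 December 2021), code it from the diagnostic angiogram where it is stored, preferably by a reader unaware of the arm. Report the number of levels actually treated by arm as a description of co-intervention, with no treatment effect estimated within it.

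The cost is one line of the analysis plan, one baseline field and a small amount of retrospective coding. No treatment rule changes.

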### Secondary objective

The secondary objective is to assess the safety of uncoated balloon catheters and test whether their efficacy is maintained across important subgroups of patients (heterogeneity of treatment effect analysis), also for surrogate outcomes of efficacy.

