### Sample size {14}

The sample size calculation is based on previous studies reporting MALE rates in PAD patients after re-vascularization procedures. These studies were heterogeneous in study design, patient selection, techniques (proportion of patients with endovascular approach), and findings [13–24]. Hess et al. reported a MALE incidence of 10% at 12 months among 381,415 re-vascularized patients that were included in the Premier Healthcare Database between April 2009 and September 2014 [19]. In addition, there were two larger interventional studies reporting 30-day MALE incidence after surgical or endovascular therapy of symptomatic PAD patients. Fashandi et al. reported a MALE incidence of 3.2% in patients with claudication at 1 month following therapy [21]. Mehaffey et al. reported a MALE incidence of 12.2% in patients with critical limb ischemia (CLI) [22]. The COMPASS trial estimated a MALE incidence of 2.0% among 6.341 patients with PAD at 21 months, of which 35% were asymptomatic. The MALE incidence was 3.6% among the subgroup of patients with previous re-vascularization procedures [24]. A subgroup analysis of the Fourier trial estimated a MALE incidence of 1.5% among 3.642 patients with PAD (31% asymptomatic) at 12 months [23]. In the XTOSI study, the 6-month amputation-free survival was 90% in patients receiving sirolimus-coated balloon catheters.

Based on these studies, assuming a 10% event rate (MALE) within 12 months in both the control and intervention group, and a non-inferiority margin of 5% expressed as absolute risk difference, a total of 1132 patients (566 patients per treatment group) allow to show non-inferiority of the intervention group with a power of 80% and a type I error rate of *α* = 2.5% one-sided. Assuming a drop-out rate of 5%, including randomization failures, a total of 1200 patients will be randomized in the study.

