## Statistical methods

### Statistical methods for primary and secondary outcomes {20a}

In the primary analysis of this trial, the absolute risk difference for MALE at 12-month follow-up between treatment groups will be estimated, together with its 2-sided 95% confidence interval. The trial statistician will perform the analyses after termination of the trial. If the overall event rate estimated at interim analysis is > 10%, an unblinded estimation of the risk difference and confidence interval will be calculated. The confidence level *α* will then be spent such that the overall type I error is preserved for an interim analysis and a final analysis, using a Lan-DeMets spending function. At interim, the confidence level will therefore be 99.95% and for the final analysis, it will be 95.05%.

If the null hypothesis concerning the primary objective is rejected (and the primary objective, non-inferiority, is thus established), further confirmatory statistical tests on primary and secondary endpoints will be performed using a pre-specified hierarchical order based on the clinical importance of the considered outcomes:

1. Superiority for the composite of unplanned (major or minor) index-limb amputations or any target lesion re-vascularization within 365 days after enrolment (*α* = 2.5% one-sided)

2. Superiority for MALE within 365 days after enrolment (*α* = 2.5% one-sided)

No additional reduction or splitting of the single *α* levels is necessary for this reason since the predefined ordering avoids any choice in the assessment (Guideline on multiplicity issues in clinical trials, European Medicines Agency; EMA/CHMP/44762/2017).

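### Subgroup effects are reported only when the interaction p-value is below 0.05, and only as ratios; this fits poorly with the secondary objective of testing whether efficacy is maintained across subgroups

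*Protocol article*

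**What the plan says.** All references are to the protocol article.

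- **Secondary objective.** The trial is to "test whether their efficacy is maintained across important subgroups of patients (heterogeneity of treatment effect analysis"). The sentence grammatically refers to the uncoated balloons. I read it as meaning the sirolimus-coated device; the wording should be reconciled.
- **Methods for additional analyses {20b}.** "The following subgroups are pre-specified for analysis of heterogeneity of effects", followed by seven factors: age, sex, Fontaine group, number of levels treated, de novo lesion or restenosis, total or partial occlusion, and distal or proximal lesion. The reporting rule comes next: "If there is evidence for a differential treatment effect within subgroups", defined as an interaction p-value below 0.05, "the treatment effect will be reported within subgroups as odds ratios or hazard ratios for time-to-event outcomes". No multiplicity adjustment is stated.
- **Statistical methods for primary and secondary outcomes {20a}.** In the primary analysis, "the absolute risk difference for MALE at 12-month follow-up between treatment groups will be estimated".
- **Sample size {14}.** The margin is 5 points, also an absolute risk difference. The calculation covers the overall comparison only, "assuming a 10% event rate (MALE) within 12 months in both the control and intervention group".

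**The concern.** Reporting is made conditional on significance. If the interaction test for a factor is not significant, the rule provides no treatment effect in either subgroup, and the reader is left with a p-value from a test the trial was not sized for. Absence of a significant interaction is not evidence that the effect is the same.

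The filter errs in both directions. A real loss in one subgroup may go unreported, and a chance interaction among seven tests may be reported.

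The scale adds a second difficulty. Non-inferiority is judged on the risk difference, but subgroup effects, when reported, are odds or hazard ratios. A reader who wants to set a subgroup result beside the 5-point margin is not given the figure for it.

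**Working it through.** **Inputs from the protocol article.** 10% MALE in both groups at 12 months, 5-point margin, one-sided α 2.5%, 80% power, 566 per group (1132 in total), 1:1 allocation; seven subgroup factors, each tested at 0.05.

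**Assumptions, not in the article.** Subgroup shares of 50%, 30%, 25% or 20%; independence of the seven tests; 10% control risk in both subgroups for the power figures.

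**1. The plan's own figure.** n per group = (1.960 + 0.842)² × 2 × 0.10 × 0.90 / 0.05² = 565.1, rounded up to 566, so 1132 in total. The stated figure is reproduced. Allowing for 5% drop-out, 1132 / 0.95 gives 1192, consistent with the stated 1200.

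**2. Power of one interaction test.** Scenario: 15% vs 10% in one subgroup (a loss the size of the margin; odds ratio 1.59, log odds ratio 0.463) and 10% vs 10% in the other.

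Power = Φ(d/SE − 1.96) + Φ(−d/SE − 1.96). SE² sums over the four cells: 1/[m p(1−p)] on the log-odds scale, p(1−p)/m on the risk-difference scale, where m is the number of patients per arm in the subgroup.

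| Share of patients in the harmed subgroup | Log-odds scale: SE, power | Risk-difference scale: SE, power |
|---|---|---|
| 50% | 0.381, 23% | 0.0375, 27% |
| 30% | 0.410, 20% | 0.0417, 22% |
| 20% | 0.465, 17% | 0.0482, 18% |

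A simpler approximation puts 10% in every cell when computing the variance. The overall SE is √(2 × 0.09/566) = 0.01783. For equal halves the interaction SE is 2 × 0.01783 = 0.0357, and power is Φ(0.05/0.0357 − 1.96) = 29%. For a 25/75 split the SE is 0.01783 × √(1/0.25 + 1/0.75) = 0.0412, and power is 23%.

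Across scales and shares, power is therefore 17% to 29%, and the chance that the subgroup effects go unreported is 71% to 83%. The log-odds column is closest to the logistic analysis in {20b}.

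**3. Dependence on the pattern.** If the rest of the trial benefits enough to make the overall difference zero, log-odds power is 81% with a 50% share (the other half then gains 5 points), 41% with 30% and 26% with 20%.

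**4. Chance findings.** With no true heterogeneity, P(at least one of seven below 0.05) = 1 − 0.95⁷ = 30%.

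**5. Scale.** The sample size section cites MALE of 3.2% in claudicants and 12.2% in critical limb ischemia. These are short-term figures from different studies and are used here only as an illustration.
- A uniform odds ratio of 1.5 gives risk differences of +1.5 points (3.2% to 4.7%) and +5.0 points (12.2% to 17.2%). There is no odds-ratio interaction, yet one group is at the margin.
- A uniform +3 points gives odds ratios of (0.062/0.938)/(0.032/0.968) = 2.0 and (0.152/0.848)/(0.122/0.878) = 1.29.

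**6. Precision if everything is reported.** The 95% CI half-width is 1.96 × √(2 × 0.09/m). With 50% of patients m = 283, giving ±4.9 points; with 30%, m = 169.8, giving ±6.4; with 20%, m = 113.2, giving ±7.8.

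**The case against.** **The objective is addressed.** It is to test heterogeneity, and interaction tests are planned for all seven factors. This stands. A reader might infer that the objective cannot be answered at all; the documents do not support that. It is answered weakly and with selective reporting.

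**The text does not bar other reporting.** It says what happens when an interaction is found, and the article condenses a fuller protocol. Participant-level data are also offered on reasonable request. This stands in part: a forest plot is not forbidden. But the article does state a conditional rule, and its natural meaning is that the other subgroup effects are not reported. That is a stated choice, not a detail left to another document.

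**Odds ratios are a natural choice here.** Logistic regression is planned for MALE, and the margin is applied only to the overall comparison. This stands as far as the test is concerned. When baseline risks differ, a constant effect on one scale is an interaction on the other, and statisticians differ on which to test. A demand to move the interaction test to the risk-difference scale is therefore not supported. Showing risk differences as well costs nothing on either view.

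**Power depends on the scenario.** This stands. A reader might infer that real heterogeneity would usually stay hidden, or that only chance findings would be published. Neither follows in general: power reaches 81% when equal halves move 5 points in opposite directions, and true interactions pass the filter too.

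**No confirmatory claim is at risk.** Correct. Subgroups lie outside the hierarchical testing order, so the primary result, error control and sample size are unaffected.

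**Conclusion.** The concern holds as a mismatch between a stated reporting rule and a stated secondary objective. Followed as written, the rule selects which subgroup effects are shown by a test with about 17% to 29% power against a margin-sized loss confined to one subgroup. That range rests on the assumed shares, a 10% control risk in both subgroups and no effect in the other subgroup. The same rule would report at least one spurious interaction about 30% of the time when nothing differs, if the seven tests are independent; correlated factors would change that figure.

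Full reporting has its own limit. With half-widths of about 5 to 8 points against a 5-point margin, subgroup estimates would be too imprecise to establish non-inferiority within each subgroup. The gain is unselected reporting on the scale of the margin, with the imprecision visible.

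**What to change.** In {20b}, replace the conditional sentence with a commitment to report, for all seven pre-specified factors and regardless of the interaction p-value:

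- event counts by arm in each subgroup;
- the MALE risk difference with 95% CI in each subgroup;
- the interaction p-value, with a note that the seven tests are exploratory and unadjusted.

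Keep the planned logistic interaction test, and keep the odds ratios and hazard ratios alongside. State that a non-significant interaction will not be read as showing maintained efficacy.

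The cost is one forest plot and a wording change. Sample size, data collection and trial conduct are unaffected.
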